|                                     |          |    | T2 Visit,
Safety check  | T4 Visit,
Safety check | T9 Visit,
data
collection | T12 Phone
call, safety
check | T15 Phone
call, safety
check | T18 Visit,
data
collection |                                                 |
| Psychological questionnaires        |          | X  |                            |                           | X                               |                                    |                                    | X                                |                                                 |
| Blood withdrawal for genetics       |          | X* |                            |                           |                                 |                                    |                                    |                                  |                                                 |
| Blood withdrawal for ACM biomarkers |          | X  |                            |                           | X                               |                                    |                                    | X                                |                                                 |
| Patient-reported outcome collection |          |    | X                          | X                         | X                               | X                                  | X                                  | X                                | X                                               |
| Study treatment adherence check     |          |    | X                          | X                         | X                               | X                                  | X                                  | X                                |                                                 |
| AE review                           |          |    | X                          | X                         | X                               | X                                  | X                                  | X                                | X                                               |
| SAE review                          |          |    | X                          | X                         | X                               | X                                  | X                                  | X                                | X                                               |

\* only if not preformed previously

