| Tertiary/Exploratory
a) Validation of prediction models of ACM progression;

b) prediction of differential response to Atorvastatin treatment. | a) Testing the prediction models on the prospectively collected clinical, biological, genetic, and radiomics data of the placebo cohort;

b) testing the association of prospectively collected clinical, biological, genetic, and radiomics data of the Atorvastatin cohort with outcome.                       | a) Verification in terms of sensitivity, specificity, overall predictive performance of the correspondence between the predicted outcome (by different prediction models) and the actual variation at T18 of the clinical, biological, genetic, and radiomics variables of the placebo cohort;

b) association coefficients of the baseline clinical, biological, genetic, and radiomics variable of the Atorvastatin cohort with endpoints outcomes.                                                                                                                                                                                                                                                                                                                                                                                                                                                                                                                                                                                                                                                                     |

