For the third objective, different AI models will be created to exploratively assess the association between a large number of potential predictors (below referred as variables) and the response to treatment, in terms of primary and secondary study endpoints. In this case, the test cohort will be

the “Atorvastatin Group”. Standard clinical variables and symptoms, together with biomarkers (as plasma lipids, inflammatory, cardiac damage and fibrosis markers), genotype and image-derived features (extracted from ECHO and CMR), collected at T0, will be taken into account as possible predictive variables to define the models. In particular, image-derived features will be obtained by radiomics analysis, which extracts a large number of quantitative characteristics that fail to be detected by the naked eye. Different models will be developed to describe the association of the previously described variables, either as single domains or combined, with the endpoint outcomes at T18 of the patients receiving Atorvastatin. Several feature selections (e.g. filter and wrapper methods) and AI algorithms (e.g. random forest, support vector classifier, k-nearest neighbors) will be used to develop multi-modal models for the prediction of response to Atorvastatin. In view of the relatively small sample size involved, a nested cross-validation approach will be used to overcome test set selection bias. The final model will be obtained by re-training the best performing pipeline in nested cross-validation on the entire dataset, with hyperparameter values tuned with a regular k-fold cross-validation on the whole dataset. Performance metrics will include balanced accuracy, sensitivity, specificity and f1 score.

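### Exploratory endpoint b is declared as association coefficients, but section 9.3 names only class-label metrics, which need a responder definition that the protocol never gives

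*Protocol*

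**What the plan says.** The Protocol's objectives tables (section 1, Synopsis, and section 4) list two exploratory endpoints with different measures.

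- Endpoint a, placebo cohort: "Verification in terms of sensitivity, specificity, overall predictive performance of the correspondence between the predicted outcome" and "the actual variation at T18 of the clinical, biological, genetic, and radiomics variables of the placebo cohort".
- Endpoint b, atorvastatin cohort: "association coefficients of the baseline clinical, biological, genetic, and radiomics variable of the Atorvastatin cohort with endpoints outcomes".

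Section 9.3 then sets out the third objective for the atorvastatin group. Its stated aim for the 18-month visit agrees with endpoint b: "Different models will be developed to describe the association of the previously described variables, either as single domains or combined, with the endpoint outcomes at" […]. It gives its methods by example, as "AI algorithms (e.g. random forest, support vector classifier, k-nearest neighbors", within nested cross-validation. On output it says: "Performance metrics will include balanced accuracy, sensitivity, specificity and f1 score".

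The outcomes to be predicted are the primary and secondary endpoints. Section 4 gives the primary one as the change in RV free wall longitudinal strain from T0 to T18. Most secondary ones are changes in volumes, thicknesses, ejection fraction, ECG intervals and biomarker concentrations. Others are counts or events, such as ventricular fibrillation and appropriate ICD shocks.

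**The concern.** Balanced accuracy, sensitivity, specificity and F1 are not association coefficients, and each is computed from a two-class outcome. Two things follow for endpoint b.

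First, the measure promised in section 4 has no counterpart among the outputs named in section 9.3. The nearest candidate there is the Pearson or Spearman correlation, but that relates endpoints to oxLDL reduction and not to the baseline variables of endpoint b.

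Second, the named metrics need a rule that turns a change in strain, volume or concentration into response or non-response, and the protocol has none. A cut on a continuous outcome discards information in an arm of about 44 evaluable patients. If it is not fixed in advance, the reported performance also depends on a choice that readers cannot verify. Section 7.4 adds to this by exempting the Aim 3 analysis from the blinded group A versus group B comparison.

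**Working it through.** **Inputs.** From section 9.1: difference 2.4 strain points, SD 4.5, one-sided α 0.05, power 80%, 44 evaluable per group. The share of patients called responders is not in the document, so it is varied as an assumption.

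**Step 1: the plan's own figure.** n per group = 2(1.645 + 0.842)² × 4.5² / 2.4² = 2 × 6.185 × 20.25 / 5.76 = 43.5, rounded up to 44. The exact one-sided t test gives 44.2, and power at 44 is 0.799. The stated 44 reproduces and is the number available to the atorvastatin-arm models.

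**Step 2: cost of splitting a continuous outcome.** For a normal outcome split so that a fraction p are responders, the asymptotic efficiency relative to the continuous outcome is φ(z_p)² / [p(1 − p)]. At p = 0.5 this is 0.3989² / 0.25 = 0.637 (that is, 2/π).

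| Responders | Efficiency | Information lost | 44 patients count as |
|---|---|---|---|
| 50% | 0.637 | 36% | 28.0 |
| 40% | 0.622 | 38% | 27.4 |
| 30% | 0.576 | 42% | 25.3 |
| 20% | 0.490 | 51% | 21.6 |
| 10% | 0.342 | 66% | 15.1 |

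The median split is the most favourable case, so 36% is the minimum loss under normality.

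**Step 3: finite-sample illustration.** 10,000 simulated data sets per setting, n = 44, one normal baseline predictor correlated r with a normal outcome, two-sided 5%. The continuous analysis is a Pearson test. The split analysis is a t test of the predictor between classes.

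| r | Continuous | 50% split | 30% split | 20% split |
|---|---|---|---|---|
| 0.3 | 0.52 | 0.34 | 0.32 | 0.28 |
| 0.4 | 0.78 | 0.57 | 0.53 | 0.46 |
| 0.5 | 0.95 | 0.79 | 0.74 | 0.66 |

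This shows the order of the loss only. Section 9.3 plans multi-predictor models judged by cross-validation, not a single-predictor test.

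**Step 4: endpoint a, by comparison of text.** Its declared measures are sensitivity, specificity and overall predictive performance, so the coefficient mismatch does not arise. It shares the missing cut-off, since its target is the variation at T18 with no threshold. It also lists genetic variables among those whose T18 variation is predicted. The schedule in section 2 marks "Blood withdrawal for genetics" at T0 only, and only if not done before. No T18 genetic measurement exists to compare.

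**The case against.** The strongest reply is that section 9.3 is open-ended. The algorithms are examples, the metrics are introduced as an inclusion list, and the stated aim is association. Random forest and k-nearest neighbours have regression forms. This stands: a reader might infer that the coefficients cannot be produced, but the text leaves them unspecified and does not exclude them.

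It can also be said that not every outcome is continuous. Ventricular fibrillation and appropriate ICD shocks are events, and class-label metrics suit them. That stands too, and it limits the point to the continuous outcomes.

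A third reply is that a responder definition may sit in a separate analysis plan. This has some force, and nothing in the protocol says that the cut will be chosen from the data. But section 9.3 says that the details of the analysis plan are described there. The point also rests on two stated items that differ, the declared measure and the named metrics, and not on the omission alone.

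A reader might also apply the decline in section 5.5 to argue severe class imbalance. With mean decline 2.4 and SD 4.5, a cut at zero would label Φ(2.4/4.5) = 70% as progressors. That describes untreated patients. If atorvastatin achieved the planned 2.4-point difference, its arm would have a mean change near zero and the same cut would split it about evenly. The 70% figure therefore does not carry over to endpoint b.

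**Conclusion.** The point holds for exploratory endpoint b: the measure declared in the objectives tables and the outputs named in section 9.3 do not match, and the named outputs depend on a responder label that is not defined. For normal continuous outcomes the cost of splitting is 36% of the information at best and about 66% at 10% responders. This range rests on normality and on assumed cuts, so no single loss figure can be attributed to the protocol.

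It would be wrong to extend the mismatch to both exploratory endpoints, because endpoint a is itself declared in terms of sensitivity and specificity. Endpoint a has only the missing cut-off and a minor wording slip on genetics; section 9.3 already uses genotype correctly, as a T0 predictor. The objective is exploratory: the primary test, the sample size and the main conclusion are untouched.

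**What to change.** In section 9.3:

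- Model continuous T18 outcomes as continuous (T18 value or change, adjusted for T0), using penalised regression and the regression forms of the named algorithms, within the nested cross-validation already planned.
- Report the association coefficients that the objectives tables promise, with cross-validated R², mean absolute error and calibration.
- Keep balanced accuracy, sensitivity, specificity and F1 for outcomes that are truly events, or as a secondary display with the cut-off for each outcome fixed before unblinding.

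In sections 1 and 4, for endpoint a, either add continuous performance metrics or fix the progression cut-off in advance. Remove genetic variables from the list whose T18 variation is predicted, and keep them as predictors.

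The cost is wording in section 9.3 and in the two objectives tables. No extra patients, visits, samples or data are needed.

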#### **9.1.1 Demographic and baseline characteristics**

Demographic and baseline characteristics will be summarized for all patients in the Safety population, by treatment group.

#### **9.1.2 Analysis of efficacy variables**

SEARCH TRIAL first aim is to provide evidence of Atorvastatin clinical efficacy in preventing ACM deterioration. The variable used to determine efficacy in the primary endpoint is the progressive decline of RV free wall longitudinal strain measured by ECHO at T18.

The variables used to determine efficacy in the secondary endpoint at T18 are i) arrhythmia burden (PVC, non-sustained and sustained VA, VF, appropriate ICD shocks); ii) other morphological parameters (ventricular volumes, function, both at ECHO and CMR); iii) ECG parameters; iv) blood parameters.

#### **9.1.3 Analysis of safety variables**

AEs will be presented in terms of the number of AE, the incidence, severity and relationship to the study drug, overall and by body system and preferred term. SAEs will be presented in the same way.

Results for routine laboratory tests will be assessed as being below the lower limit of the normal range, within the normal range or above the upper limit of the normal range. The frequency of patients reporting an abnormal or abnormal clinically significant laboratory value at screening and follow-up will be presented for each laboratory variable. Vital signs will be presented using descriptive statistics.

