### 3.3. Benefit/Risk Assessment

If the hypothesis proves to be correct, we expect to slowing down disease progression, both from the tissue and the electrical points of view, and consequently an improvement in symptoms and a reduction in arrhythmic risk.

The proposed therapy is expected to bring significant clinical benefit compared to existing therapies in Arrhythmogenic Cardiomyopathy context, none of which targets the fibro-adipogenic disease progression. The use of statins in patients suffering from ACM may have beneficial effects in reducing the progression of the pathology and avoiding the most severe consequences of the disease. Indeed, beyond the described canonical lipid-lowering effects, atorvastatin has known pleiotropic effects, as anti-oxidant, anti-inflammatory and anti-arrhythmic, leading, in ACM patients, to lowering of the triggering factor oxLDL, reduction of the inflammatory mediated disease bursts, and moderation of the arrhythmia burden.

The expected results will be beneficial for the health system, reducing costs and efforts for the management of ACM patients.

In addition, the patient in the study will be guaranteed close follow-up and more in-depth care than during routine visits.

However, it is possible that a subgroup of patients taking Atorvastatin may experience side effects.

In the database of placebo-controlled atorvastatin clinical trials involving 16,066 patients (8755 Atorvastatin vs. 7311 placebo) treated for an average period of 53 weeks, 5.2 per cent of patients on atorvastatin discontinued the trial due to adverse reactions, compared to 4.0 per cent of placebo-treated patients.

Below is the profile of atorvastatin adverse reactions based on data from clinical studies and extensive post-marketing experience. The frequencies of the estimated reactions are classified according to the following convention: common ( $\geq 1/100$ ,  $< 1/10$ ); uncommon ( $\geq 1/1,000$ ,  $< 1/100$ ); rare ( $\geq 1/10,000$ ,  $< 1/1,000$ ); very rare ( $< 1/10,000$ ); frequency unknown (cannot be defined based on available data).

Infections and infestations

Common: nasopharyngitis.

Haemolymphopoietic system disorders

Rare: thrombocytopenia

Immune system disorders

Common: allergic reactions

Very rare: anaphylaxis

Metabolism and nutrition disorders

Common: hyperglycaemia

Uncommon: hypoglycaemia, weight gain, anorexia

Psychiatric disorders

Uncommon: nightmares, insomnia

Nervous system disorders

Common: headache

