| Secondary
a) Efficacy of Atorvastatin in avoiding electric, morphological and biomarkers deterioration;

b) safety of Atorvastatin treatment   | a) Deterioration from baseline of
i) arrhythmia burden (PVC, non-sustained and sustained VA, VF, appropriate ICD shocks); ii) other morphological parameters (ventricular volumes, function, both at ECHO and CMR); iii) ECG parameters; iv) blood parameters;

b) monitoring of AE and patient's well-being. | a)
i) Deterioration from baseline of the frequency of premature ventricular contractions, non-sustained and sustained ventricular arrhythmias, episodes of ventricular fibrillation, appropriate defibrillator shocks (measured by Holter, defibrillator and loop recorder interrogation at T18).
ii) Variation from baseline of morphological parameters, such as ventricular volumes (ml), parietal thicknesses (mm), fibrotic replacement characteristics (mm  ), cardiac functional parameters as ejection fraction (%) or Fractional shortening (%), heart movements (number and extension of bulging and wall motion abnormalities) measured at ECHO and CMR at T18.
iii) Variation from baseline of the electrocardiogram parameters (ms or voltage) at T18.
iv) Variation from baseline of biomarkers at T18 (concentrations, Units).
b)
i) Number and severity of adverse events (blood safety parameters variation and number and severity of patient-reported adverse effects) till T18.
ii) Variation in the score of the psychological questionnaires at T18 respect to baseline. |

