## 9. Statistical Considerations

### 9.1. Sample Size Determination

A power analysis estimated that 88 patients (44 per group) will be sufficient to observe at T18 a significant ( $\alpha=0.05$ ) mean absolute difference between the two groups of 2.4 points of RV free wall longitudinal strain (%), hypothesizing a standard deviation of 4.5% and with a power of 80%. The statistical test used to calculate the sample size was an independent one-sided T test. Assuming a drop-out rate of 15% during the study, the total sample size is 102 patients (51 per group). Assuming a screening failure of about 5%, 110 patients will be screened.

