### 9.2. Populations for Analyses

The Safety population will consist of all patients who received any study medication and will be based on the treatment actually received. The Safety population will be used to present the demographic and baseline data, and all safety data.

The Intent to Treat (ITT) population will consist of all patients who are randomized and receive the IMP (either Atorvastatin or placebo); it will be based on the treatment randomized, regardless of the treatment actually received. The ITT population will be used to present efficacy data.

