#### **9.1.4 Missing data**

All reasonable efforts will be made to reduce the rate of missing data, since any method used for imputation for missing observations would be based on untestable assumptions.

In case of impossibility of performing CMR in some patients, the patients will be excluded from the analysis of the specific elements, based on CMR, of the secondary endpoint. The same parameters acquired by ECHO will be used.

Investigators will be trained about the importance of patient retention and full data capture. Also, any reasonable attempts should be made by the Investigators to emphasize continued patient's participation for the full duration of the trial. However, in order to minimize missing data, if a patient cannot refer to the site for a planned follow-up visit, the Investigator will try to obtain any relevant

information from the patients, including documents/laboratory results available from local medical care.

However, if a patient is lost at follow-up after the T9 data collection visit, imputation of missing data may be implemented, when possible, followed by sensitivity analyses.

If the patient drops-out before T9 the patient will be simply excluded from the analysis.

We expect that a larger number of patients will abandon the study if they are in the Atorvastatin group, respect to the Placebo one, since they have probability to experience atorvastatin-related adverse effects. The 15% drop-out rate described in the sample size calculations, takes into account this possibility.

An effort will be made to understand the reasons of drop-outs, mainly to assess whether they are related to the outcomes (ACM-linked events). In this case, to avoid a possible bias (the most serious patients abandon the study) a post-hoc statistical correction may be implemented.

We will try to reduce unused data (collected data items that will not directly link to a result and will therefore not be counted in the final manuscript), and spurious data or spurious inferences, to improve study performance, lower time and costs of collection and storage, and address ethical concerns.

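### Raw AE counts and an undefined incidence ignore observation time, although the plan expects more patients to leave the study on atorvastatin

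*Protocol*

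**What the plan says.** - **Endpoint.** Secondary endpoint (b)(i) in section 4 is "Number and severity of adverse events" up to T18.
- **Summary.** Section 9.1.3 says "AEs will be presented in terms of the number of AE, the incidence, severity and relationship to the study drug", in total and broken down by system and term, with SAEs handled alike. It gives no person-time denominator, no time-to-event summary and no definition of incidence.
- **Denominator.** The Safety population in section 9.2 is "all patients who received any study medication", so a patient who leaves early still counts as one full patient.
- **Drop-out by arm.** Section 9.1.4 says "We expect that a larger number of patients will abandon the study if they are in the Atorvastatin group, respect to the Placebo one", and gives the reason: "since they have probability to experience atorvastatin-related adverse effects". It states no split. Section 9.1 assumes 15% overall, with 51 patients per group.
- **Only figures by arm.** Section 3.3 reports, for earlier placebo-controlled atorvastatin trials with a mean duration of 53 weeks, that "5.2 per cent of patients on atorvastatin discontinued the trial due to adverse reactions, compared to 4.0 per cent of placebo-treated patients".
- **Observation.** Section 8.3 collects AEs from consent to the end of the study. Stopping the tablets alone therefore does not end observation; leaving the study does.

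**The concern.** A count of events up to month 18 is comparable between arms only if the arms are watched for about the same time. Section 9.1.4 foresees that they will not be, and in which direction. A patient who leaves at month 4 adds one to the denominator but can contribute only four months of events, and more such patients are expected on atorvastatin.

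The safety of atorvastatin in this new indication is a stated secondary objective, so the arms' AE columns will be read side by side. Nothing in section 9.1.4 deals with this. It covers imputation after T9, exclusion of patients lost before T9, and a possible later correction for exits linked to the disease. None of these concerns time at risk for AEs.

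**Working it through.** The protocol states no exposure time or AE rate, so there is no figure of its own to reproduce on this point. Its 51 per group is 44 × 1.15 = 50.6, rounded up. Arm size cancels from the ratios below.

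**Step 1. Total counts.** Let *d* be the share of an arm that leaves and *m* the fraction of the 18 months that leavers complete on average.

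Mean months observed = 18 × (1 − *d*(1 − *m*)).

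If the true AE rates are equal and constant, and leaving is unrelated to AEs, the expected ratio of raw counts equals the ratio of mean months. The splits are assumptions chosen to average 15%. The first row is the 1.2-point gap of section 3.3 (5.2 − 4.0) centred on 15%. Leaving spread evenly over the period means *m* = 0.5; leaving at month 2 means *m* = 1/9.

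| Leave: atorvastatin vs placebo | Months, even leaving | Count ratio | Months, leaving at month 2 | Count ratio |
|---|---|---|---|---|
| 15.6% vs 14.4% | 16.60 vs 16.70 | 0.994 | 15.50 vs 15.70 | 0.988 |
| 17% vs 13% | 16.47 vs 16.83 | 0.979 | 15.28 vs 15.92 | 0.960 |
| 20% vs 10% | 16.20 vs 17.10 | 0.947 | 14.80 vs 16.40 | 0.902 |
| 25% vs 5% | 15.75 vs 17.55 | 0.897 | 14.00 vs 17.20 | 0.814 |
| 30% vs 0% | 15.30 vs 18.00 | 0.850 | 13.20 vs 18.00 | 0.733 |

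Example: for 20%, even leaving, 18 × (1 − 0.20 × 0.5) = 16.2; for 10%, 18 × (1 − 0.10 × 0.5) = 17.1; and 16.2/17.1 = 0.947.

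**Step 2. Share of patients with an event, when leaving is unrelated to it.** Take an exponential time to first event with an 18-month risk of 30%, so 18λ = −ln 0.7 = 0.357. Leavers spread evenly have an observed risk of 1 − 0.30/0.357 = 0.159. With 20% versus 10% leaving:

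- atorvastatin: 0.8 × 0.30 + 0.2 × 0.159 = 0.272
- placebo: 0.9 × 0.30 + 0.1 × 0.159 = 0.286
- observed risk ratio 0.95, where the truth is 1.00.

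If the hazard on atorvastatin is 1.5 times as high, the true risk ratio is 1.38 and the observed one 1.32. This is the relevant case for an event type that does not itself cause the exit.

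**Step 3. Leaving prompted by an AE, the reason section 9.1.4 gives.** This was simulated with 400,000 patients per arm and equal true AE rates. Both arms had 10% background drop-out; on atorvastatin there was an added chance of leaving after each AE.

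| AEs per 18 months; chance of leaving after each | Any AE | Mean count (ratio) | Rate per 18 months observed |
|---|---|---|---|
| 2; 6.5% | 83.6% vs 83.4% | 1.785 vs 1.899 (0.94) | 2.003 vs 1.999 |
| 1; 12% | 60.6% vs 60.6% | 0.897 vs 0.948 (0.95) | 1.002 vs 0.998 |

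Drop-out came out at 21.1% and 20.2% on atorvastatin against 10% on placebo. The share with any AE does not move, because the patient who leaves has already been counted. The total count falls by 5 to 6%, and the exposure-adjusted rate recovers the true ratio of 1.00.

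**The case against.** **A reader might infer that the plan makes atorvastatin look safer in general.** The documents do not support that. The stated reason for leaving is an adverse effect that has already been recorded. Step 3 shows that the share of patients with any AE is then essentially unbiased. Worse tolerability also adds counted events, so it does not follow that the understatement grows steadily as tolerability worsens.

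**A reader might also infer that leavers are expected mainly on atorvastatin.** Section 9.1.4 says only that there will be more of them there. The one pair of figures by arm, in section 3.3, gives a 1.2-point gap and a distortion of about 1%. Those figures cover adverse-reaction discontinuation over a mean of 53 weeks. Scaling the gap in proportion to 18 months (78 weeks) gives 1.2 × 78/53 = 1.8 points, which is still small. The 20% versus 10% split has no source in the protocol. For scale, with 51 per arm and an assumed AE share of 20 to 80%, the 95% half-width on a difference is already about 16 to 19 points.

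**Other objections that carry weight:**
- Section 9.1.3 says AEs are presented and states no test between arms.
- Incidence is undefined and could already mean a rate.
- Scaling counts by months assumes constant risk. If drug-related events cluster early, an early leaver loses fewer events than the table implies.
- Serious events thought related to the drug are reportable without time limit (section 8.3.3), and SAE follow-up can run past study exit (section 8.3.3.1). The loss is therefore smaller for these.
- Exposure-adjusted tables are often left to a separate analysis plan. Section 9.3 weakens this, since it says the analysis plan is the text that follows it.

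These points limit the size and reach of the concern. They do not remove it for total counts or for event types that do not prompt the exit.

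**Conclusion.** The point holds in a limited form and is minor. The safety endpoint is a count to a fixed month, early leavers stay in the denominator, and the protocol itself expects unequal leaving. Total AE counts, and the incidence of later or other event types in the detailed tables, may therefore understate risk on atorvastatin relative to placebo. The share of patients with any AE is largely unaffected if the AE prompts the exit.

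The understatement of counts is about 1% for a 1.2-point gap. It is about 5% (even leaving) to 10% (leaving at month 2) for an assumed 20% versus 10% split. Larger values need splits that nothing in the protocol suggests. All these figures rest on a constant AE rate and an overall drop-out of 15%.

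**What to change.** In section 9.1.3:

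1. Define incidence as the share of patients with at least one event.
2. Show patient-months of observation by arm.
3. Add exposure-adjusted AE and SAE rates (for example per 100 patient-months) with 95% confidence intervals.
4. For muscle and liver events, add cumulative incidence by time since first dose, censored at study exit.
5. Keep the planned counts and percentages as description.

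The cost is a few extra table columns and no new assessments. AE start dates are already recorded (section 8.3.2), as are dispensing dates (section 7.5.3), and withdrawals must be documented (section 8.2.3). The sponsor need only confirm that the eCRF holds the dates of first dose and of study exit. The drawback is that a single rate assumes roughly constant risk, so it should be read together with the cumulative incidence.
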